## Abstract

**Background:**

We designed a program for prehabilitation and education before a shoulder replacement (PREPS) that is based on reviews of relevant literature, and is co-designed with preferences of patients recruited from the wait list for a shoulder replacement, and a transdisciplinary healthcare sample. The content and format was integrated in a comprehensive, patient-centered program combining exercise, preparedness for surgery, motivational interviewing, and pain management principles. This patient-centered program has the potential to improve postoperative pain, function, and patient-oriented outcomes, decrease postoperative opioid use and short- and long-term healthcare costs. This pilot randomized controlled trial will evaluate feasibility and satisfaction with our program for individuals undergoing a shoulder replacement.

**Methods:**

Participants (*n* = 90) undergoing a shoulder replacement will be randomized into (1) a 6-week self-directed online pre-rehab and education program, (2) a 6-week online pre-rehab and education program with a therapist to monitor progression of PREPS or (3) a standard of care group. The PREPS program intervention groups will be delivered virtually with an online program of modules and a written handbook. Feasibility outcomes include recruitment rate, adherence, content acceptability, study acceptability, outcome measure completion rates and treatment fidelity. Outcomes will be assessed at baseline and 1 day before surgery, then post-operatively at 6 weeks and 3,6 and 12 months.

**Discussion:**

The proposed project will include the feasibility testing of a prehabilitation and education program with potential to improve surgical outcomes for shoulder replacement patients. Results of this study will provide the foundation for a future fully powered multicenter trial.

**Trial Registration:**

NCT05965986.

## Introduction

A total shoulder arthroplasty (TSA) is a standard operative treatment for a variety of glenohumeral joint conditions, such as shoulder osteoarthritis.^
1
^ Individuals who experience continued shoulder pain and loss of function, despite conservative management, often undergo a TSA. The overall outcomes of a TSA are quite good with respect to restoring function of the glenohumeral joint,^
2
^ which is attributed to many factors, including severity of the underlying pathology, surgical technique, and adherence to post-surgery rehabilitation.^1–3^

While the outcomes of TSA are favourable, the surgical procedure can be stressful for patients and their caregivers. Previous research has shown that patient education prior to surgery can lead to better postoperative outcomes and experience for the individual.^4–6^ Education prior to surgery allows sufficient time to process information, or to share information with caregivers and may set more realistic expectations and support less decisional conflict for patients. The concept of preoperative education has been used to increase patient knowledge and behavior change across various surgical procedures.^4–6^

While elective orthopedic surgeries have adopted the concept of preoperative education, there remains a lack of consensus around the key content, delivery, timing of administration and expected outcomes. Further, there is a large amount of literature focused on patient education in lower limb joint replacement surgeries, but a lack of literature addressing upper limb replacement surgeries: the generalizability of treatment effects is unclear. Further, the COVID-19 pandemic uncovered the need for alternative delivery models that maintain social distancing, such as virtual programs. A remote preoperative education program can address barriers to access, ensure information is consistently communicated, and provide individuals an option for repeated reviewing as desired and/or needed.^7–9^

We have developed a comprehensive, patient-centered program that combines exercise, preparedness for surgery, motivational interviewing, and pain management principles.^10,11^ The program is titled Pre-Rehab and Education Program before Surgery (PREPS). The intervention was developed in collaboration with patient partners on the wait list for a shoulder replacement, a transdisciplinary healthcare team (i.e., surgeons, physiotherapists, occupational therapists, and rehabilitation researchers), and current scientific literature. This patient-centered prehabilitation program has the potential to improve postoperative pain, function, and patient-oriented outcomes, and decrease postoperative opioid use and long-term healthcare costs.

Prior to testing the effectiveness of the intervention in a fully powered randomized controlled trial (RCT) we aim to complete a pilot randomized controlled trial to test the feasibility of the intervention and study protocol. Primary feasibility outcomes will be recruitment and retention of patients, given the challenges when sampling an older adult population. Additionally, we anticipate some technological challenges given the intervention will primarily be delivered virtually.

The study will aim to answer the following research questions:1. What is the acceptability and satisfaction with the PREPS program for patients undergoing a total shoulder replacement?2. How feasible is the PREPS program in terms of recruitment rate, adherence rate, retention rate, and participant burden?3. What outcome measures tested in the feasibility trial should be included within the full RCT?

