### Participants

We will recruit volunteers over the age of 18 years, who have been consented for a shoulder replacement surgery at the HULC, to fulfill a sample size of 90 participants, with 30 in each arm. The sample size is based on current recommendations for pilot studies, objectives of this study, and feasibility of being able to complete recruitement of the full powered trial in 2 years. Since our sample size is 168 in the full powered trial, we aim to collect half of this in 1 year. See below for full trial sample calculation.

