### Outcomes

All participants, regardless of group will complete all study visits (consisting of 2 pre-operative visits [baseline and one day before surgery] and post-operative visits at 6 weeks, 3 months, 6 months and 1 year). At baseline, we will collected demographic characteristics such as: sex, height, weight, reason for surgery, symptom duration, affected shoulder, and dominant hand. In the pilot study, we will test all outcomes to determine which measures will be moved forward to the full study.

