#### Outcomes to be included within the full study

The following outcomes listed below will be included in the pilot study since participants in the pilot may be rolled into the full study (see Table 1). The primary outcome in the full study will be the SPADI and secondary outcomes will include:• *General health status* as measured by EQ-5D global health^
13
^ and Single Assessment Numeric Evaluation^
14
^• *Shoulder specific function tests*: American Shoulder and Elbow Surgeon’s Score,^
15
^ Shoulder Pain and Disability Index,^
16
^ Simple Shoulder Test^
17
^• *Patient satisfaction*: Surgical Satisfaction Questionnaire (SSQ-8)• *Patient Anxiety *as measured by the Decisional Regret Scale,^
18
^ and Patient Anxiety Symptom Scale (PASS)• *Adherence to rehabilitation* as recorded in the patient log (see Table 1)• *Performance measures*: goniometric measures of shoulder range of motion

**Table 1. table1-17589983251345393:** DRS, decisional regret scale; SPADI, shoulder pain and disability index; SANE, Single assessment of the numeric evaluation; PPQ, patient participation questionnaire; SSQ-8, surgical satisfaction questionnaire; SAQ, surgical anxiety questionnaire.

Variable/outcome	Hypothesis	Outcome measure	Method of analysis
Recruitment	15-16/ month And 50% eligible to participate	Research log	Percentages reported

Adherence	80% of all participants in the intervention groups complete the PREPS program, and 60% report exercise at least 3 times per week	Patient log	Percentages reported
Content acceptability	60% of participants found the treatment useful and helpful on item 7	Surguical satisfaction quesionnaire	Means and standard deviation reported
Study acceptability	60% of participants found the treatment delivery acceptable, and reported being likely to use this treatment again and recommend it to others, on item 10	Surguical satisfaction quesionnaire	Means and standard deviation reported
Treatment fidelity	If 80% of phone calls and recorded notes were documented on the checklist by the therapist	Therapist checklist	Means and standard deviation reported

The majority of assessments will occur at baseline, day before surgery, and post-surgery at 6 weeks, 3 months, 6 months and 12 months. With the exception of some measures, as detailed in Figure 1, of the schedule throughout the research study.

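### The question of which measures enter the full trial has no decision rule, and the progression criteria omit retention and outcome completion, which the article itself names as feasibility outcomes

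*Protocol article*

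**What the plan says.** The Introduction's third research question is "What outcome measures tested in the feasibility trial should be included within the full RCT". The Outcomes section repeats the intention: "In the pilot study, we will test all outcomes to determine which measures will be moved forward to the full study".

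The next-but-one subsection, headed as the outcomes to be included within the full study, reads as if the choice were made. It states "The primary outcome in the full study will be the SPADI and secondary outcomes will include" and then gives a named list. Its reason for collecting them is roll-in: "The following outcomes listed below will be included in the pilot study since participants in the pilot may be rolled into the full study".

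The Methods part of the Abstract ends its list of feasibility outcomes with "study acceptability, outcome measure completion rates and treatment fidelity". The Introduction names recruitment and retention as the primary feasibility outcomes, and its second research question asks about the retention rate.

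The Plan for statistical analyses judges each primary feasibility outcome separately against Table 2 and lets the worst one decide. All green means going on to the definitive trial with no change. Amber means amending the procedures first. Red means substantial revision and a new assessment of feasibility.

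Sample size estimation uses an ANCOVA formula with the correlation between baseline and 3-month SPADI. It arrives at 53 per group, raised by 5% to 56.

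**The concern.** A pilot that sets out to choose outcome measures needs evidence on how well they are completed and a rule that uses it. Here the completion rate is announced and then disappears before the criteria are set. Retention, announced as primary, disappears too. The rule that remains is specific about its consequences, so the gap could change a decision: SPADI data could be largely missing at 3 months while every Table 2 row is green.

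The definitive trial depends on that figure. Its sample size allows for 5% loss, and the pilot collects the data that would test this allowance, but no criterion looks at them. The article also leaves unclear which measures are open to change, so nobody can say in advance what finding would drop one.

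**Working it through.** **1. Where each feasibility outcome appears in the article**

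| Outcome | Abstract | Introduction | Feasibility outcomes list | Table 1 | Table 2 |
|---|---|---|---|---|---|
| Recruitment | yes | yes (primary) | yes | yes | yes |
| Adherence | yes | yes | yes | yes | yes |
| Content and study acceptability | yes | yes (acceptability) | yes | yes | yes |
| Treatment fidelity | yes | no | yes | yes | yes |
| Outcome measure completion | yes | no | no | no | no |
| Retention | no | yes (primary) | no | no | no |

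The last two rows have no threshold anywhere. Any value from 0 to 100% is compatible with all green.

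**2. The plan's own sample size**

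Inputs from Sample size estimation: one-sided alpha 0.05 (z = 1.64), power 0.80 (z = 0.84), SD 21.3, r = 0.81, difference 10.3, margin 4.26.

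n = 2 × (1.64 + 0.84)² × 21.3² × (1 − 0.81²) / (10.3 − 4.26)² = 52.6, so 53 per group. Then 53 × 1.05 = 55.7, so 56 per group, and 3 × 56 = 168, as the Participants section states. The figure reproduces and is not in dispute.

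**3. What lower completion would cost**

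Residual SD = 21.3 × √(1 − 0.81²) = 12.49. Power = Φ(6.04 / (12.49 × √(2/n)) − 1.645), with n the number analysed per group.

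| Completion | Analysed per group | Power |
|---|---|---|
| 53/56 = 94.6% | 53 | 80% |
| 80% | 0.80 × 56 = 44.8 | Φ(2.289 − 1.645) = 74% |
| 60% | 0.60 × 56 = 33.6 | Φ(1.982 − 1.645) = 63% |

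This assumes that participants without a score drop out of the analysis and that missingness is unrelated to outcome.

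**4. Open or fixed?**

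The Introduction and Outcomes sections say the measures are to be determined from the pilot. The later subsection names the SPADI as primary and lists the secondaries under a heading that places them in the full study. The wording conflicts, and the article does not say which text governs.

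**5. Timing**

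The Participants section refers to "feasibility of being able to complete recruitement of the full powered trial in 2 years" and aims for half of the 168 in one year. Surgery is at least 9 weeks after entry (2.07 months), and the last visit is 12 months after surgery. Steady accrual and surgery at exactly 9 weeks are assumed. Counted from first pilot enrolment, the last 12-month visit falls at:

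- 90 at 15 per month (lower end of the Table 2 green rate): 6 + 2.07 + 12 = month 20.1
- 90 in 12 months (Table 2 row label): 12 + 2.07 + 12 = month 26.1
- 90 in 24 months (feasibility outcomes list): 24 + 2.07 + 12 = month 38.1

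At 12-month accrual, (24 − 14.07)/12 × 90 = about 74 of 90 participants have 12-month data by month 24. If the 2 years begin only after a 12-month pilot, they run from month 12 to month 36, and month 26.1 falls inside them.

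**The case against.** The strongest reply is that choosing measures is a judgement on completion, burden and measurement performance. It need not be a traffic-light row, and selection criteria for secondary measures are detail that an article may leave to the full protocol or analysis plan. That stands for the detailed criteria. It does not cover the progression rule, which the article publishes with fixed consequences and which omits an outcome the article calls primary.

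A second reply is that the rule covers primary feasibility outcomes only, and completion is never called primary. That is correct, and it makes retention the clearer omission. One row can serve both.

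A reader might go further and infer that the third research question cannot be answered, or that no result could remove a measure. The text does not support this. The Outcomes section expressly allows for choosing among the measures, and dropping one later is compatible with roll-in. Completion data to 3 months will exist for every visit attended.

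A reader might also infer that the 12-month data arrive only after full-trial recruitment has ended. That requires the 2-year clock to start at first pilot enrolment, with no pause between pilot and full trial. The article does not say so: it makes proceeding conditional on the pilot and says only that participants may be rolled in. Even with that start, the last visit comes before month 24 at 15 per month, and at 12-month accrual most 12-month data are in by then.

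**Conclusion.** The point holds as a gap in the decision rule. Retention and outcome completion are named as feasibility outcomes but have no criterion, so the stated rule can send an under-completed pilot forward unchanged. The illustrated cost is a fall in power from 80% to about 74% at 80% completion and about 63% at 60%, on the plan's own inputs and under the missing-data assumptions stated. These completion rates are illustrations; the article gives no expected rate other than the 5% loss.

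The conflict over whether the measure list is open or settled is one of wording and is easily repaired. On timing, only a conditional statement is justified: if pilot participants are rolled in and the 2 years count from first pilot enrolment, complete 12-month data may come too late to guide the choice. It is worth correcting before the progression decision is taken.

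**What to change.** Add one row to Table 2 for retention and SPADI completion at 3 months, the visit whose correlation enters the sample size.

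- **Green:** tied to the plan's own loss allowance, about 95% (53 of 56; in a pilot of 90, 53/56 × 90 = 85.2, so at least 86).
- **Amber:** below that, with the loss allowance and sample size recalculated from the observed rate before proceeding.
- **Red:** below a lower limit that the sponsor sets in advance.

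Borrowing the 80% used for adherence and fidelity would not do. Table 2 has no single scale (acceptability is green at 60%), and an 80% green would pass about 45 per group against the 53 required.

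Add retention and completion to the list of feasibility outcomes and to Table 1. Relabel the secondary list as candidate measures. State that completion at each measure's scheduled visits informs which are kept, since not all are collected at every visit, and name the visit at which the choice is made. Say whether the 2-year period includes the pilot, and reconcile the 12-month, 24-month and 15–16 per month recruitment figures.

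The cost is some protocol wording and one descriptive table from data already collected. The downside is one more criterion that may turn amber, and a choice of measures that rests on the earlier visits.

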## Methods and analysis

### Study design

This study describes a design of a single center, parallel-group RCT (1:1:1 ratio) to be conducted at the Roth|McFarlane Hand and Upper Limb Centre (HULC) in London, Ontario. HULC is a tertiary care center specializing in the management of complex upper limb disorders and conditions. HULC sees over 40,000 patients per year, and is one of the leading sites for shoulder replacement surgeries in Ontario. The program itself will take place online, with patients being able to engage with the program at their homes.

### Trial design

The pilot study will be a single-blinded randomized trial with three intervention groups. Participants will be randomized to either:1. A group consisting of the PREPS program 6 weeks before surgery2. A group consisting of the PREPS program 6 weeks before surgery + therapist following3. A group consisting of the current standard of care at HULC, which is a WebEx (online synchronous) pre-operative education class lead by a physiotherapist and occupational therapist.

There will be a one-to-one allocation ratio. Groups will be stratified by biological sex (male/female) and replacement type (reverse or anatomical), using a web-based randomization software. The sample size was designed based on multiple papers and criteria for pilot studies and to provide sufficient data to pilot our disaggregated sex/gender-based analyses (SGBA) plan.^
12
^ Given the predominance of women in this population, we will specifically recruit men to ensure that at least 40% of participants are men, to support SGBA. Allocation will be concealed until eligibility is fully determined. All outcome measures will be performed by a X evaluator.

### Participants

We will recruit volunteers over the age of 18 years, who have been consented for a shoulder replacement surgery at the HULC, to fulfill a sample size of 90 participants, with 30 in each arm. The sample size is based on current recommendations for pilot studies, objectives of this study, and feasibility of being able to complete recruitement of the full powered trial in 2 years. Since our sample size is 168 in the full powered trial, we aim to collect half of this in 1 year. See below for full trial sample calculation.

#### Inclusion criteria

• Over the age of 18 years• Patients who have consented for a total shoulder arthroplasty or reverse shoulder arthroplasty surgery at HULC• Date of surgery must be no sooner than 9 weeks, to ensure time for baseline measures• Speaks and reads in English• Able to provide informed consent• Willing to participate in study procedures for at least 1 year post-surgery

#### Exclusion criteria

• Patients who have consented for a hemi-arthroplasty surgery• Any contraindications to exercise• Patients with medical conditions that preclude participation in the sessions or follow-up

### Patient and public involvement

Previous work was done by our group to survey patients on the wait list for a shoulder replacement surgery and clinicians with experience treating patients undergoing a shoulder replacement to better understand preferences of implementing a preoperative online program. Figure 1 details the intervention map used to create PREPS. Patient partners were consulted about the online program to inform feasibility, patient burden and relevance. Future sub-studies will investigate patient engagement and usability with the intervention.^21,22^

**Figure 1. fig1-17589983251345393:**
[figure not shown]
Intervention mapping for PREPS program.

### Recruitment procedure

The overall flow of the trial is described in Figure 2. Patients who are referred to the HULC and meet the eligibility criteria, will be invited to participate in the study. Clinicians and research staff are trained on the recruitment procedure to maximize the recruitment rate. Information and initial recruitment about the study will be made by the attending surgeon. If patients are interested, a research associate will follow up with the patient to provide additional study details and/or answer questions. Patients will have sufficient time to review study related documents before providing written consent to be enrolled in the study.

**Figure 2. fig2-17589983251345393:**
[figure not shown]
The schedule of enrolment, interventions and assessments for PREPS trial.

### Randomization and concealment of allocation

Patients who are eligible and have consented, will be randomized by a 1:1:1 before their baseline assessment. *A priori*, the principal investigator (JM) will prepare the randomization sequence through computer- generated software, stratifying for sex and implant type, to ensure groups are balanced on these important prognostic factors. Allocation assignments will be sealed in a numbered, opaque envelope prepared by the research associate. Envelopes will be accessed only after patient consent has been obtained. 

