### Blinding

The lead student investigator will not be blinded to participant allocation, and so any follow up visits and testing will be conducted by a blinded research assistant. The therapist who will follow patients randomized to Group 2 will not be blinded as they will only have access to patients in Group 2.

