#### Comparator

The control group will not receive the new preoperative program. They will participate in the standard of care at the HULC, which consists of regular appointments with their surgeon, check-ins with the pre-admit staff at HULC, and the webinar class with a physiotherapist and occupational thereapist. This webinar class, is a one time class with both anatomical and reverse shoulder replacement patients: caregivers are also welcomed. The class consists of two parts, part one focuses on the anatomy of the shoulder, some aspects of the surgurical procedure and anaesthesia information led by a physiotherapist. Part two focuses on how to prepare your environment for after surgery such as clothing, bathing and sleeping, lead by an occupational therapist. The class is an hour long, on an online synchronous platform, and runs monthly. Patients are requested to attend the class once prior to surgery.

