## Sample size estimation

Our sample size calculation will be based on a formula for analysis of covariance (ANCOVA), with an estimated association between preoperative and postoperative SPADI scores at 3 months.^
19
^ Correlation of SPADI scores from baseline and 3 months will be determined from pilot trial findings, however, we have estimated a calculation based on current literature of the SPADI in arthroplasty patients.^19,20^

Calculation: N per group = 2((Z_α_ + Z_β_)^2^σ^2^(1-r^2^))/(δ-M)^2^, where:

α = the probability of making a Type I error = 0.05, one-sided test

1-β = the power to detect a difference if one truly exists = 0.80, thus, β = 0.20

δ = MCID (within-group) = 20.6, adjust for between-groups comparisons 20.6*0.5 = 10.3

r = at 3 months = 0.81

σ = 21.3 (SD at 1 year post-operative)^
20
^

M = 0.2 SD (4.26), margin for non-inferiority (Group 1 v Group (2) and superiority (Group 1 v SOC)

N per group = 2((1.64 + 0.84)^2^ (21.3)^2^(1-0.81^2^))/(10.3-4.26)^2^ = 53 patients per group

The estimate per group will then be increased by 5% to adjust for potential losses over time (*n* = 56/group).

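### Randomisation is placed before the baseline assessment with no safeguard against disclosure, so baseline SPADI, the covariate of the full trial's planned ANCOVA, may be reported with knowledge of the arm

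*Protocol article*

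**What the plan says.** The order of events is explicit. Under Randomization and concealment of allocation: "Patients who are eligible and have consented, will be randomized by a 1:1:1 before their baseline assessment". The same section makes consent the only condition for opening the envelope: "Envelopes will be accessed only after patient consent has been obtained". Trial design ends concealment at a different point, but also not at completion of baseline: "Allocation will be concealed until eligibility is fully determined".

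On blinding, Trial design says "The pilot study will be a single-blinded randomized trial with three intervention groups". The Blinding section names a blinded research assistant ("any follow up visits and testing will be conducted by a blinded research assistant") and does not say that participants are blinded. The arms are plainly distinguishable: an online programme with booklet, the same plus therapist phone calls, or the usual class. The Comparator section adds that "The control group will not receive the new preoperative program".

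The Sample size estimation section bases the full trial on a "formula for analysis of covariance (ANCOVA), with an estimated association between preoperative and postoperative SPADI scores at 3 months", and says that the baseline to 3-month correlation will come from the pilot. The section on outcomes for the full study makes SPADI its primary outcome and allows pilot participants to be carried over into it. The inclusion criteria require "Date of surgery must be no sooner than 9 weeks, to ensure time for baseline measures".

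**The concern.** Adjusting for a baseline score is safe because allocation cannot have influenced that score. Measuring it before allocation is known guarantees this; the order fixed here gives the guarantee up. A participant who has learned the arm may answer a baseline questionnaire differently, out of disappointment or expectation. A blinded assessor does not protect an answer that the participant supplies.

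Two consequences are possible. First, a between-arm shift in reported baseline SPADI passes through the ANCOVA into the adjusted treatment effect. Second, a patient who withdraws after learning the arm but before baseline is randomised with no covariate value, and such losses may be unequal between arms. If pilot participants join the full trial, baselines collected in this order cannot be re-collected.

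**Working it through.** **Does any passage close the gap?** Set side by side, randomisation precedes baseline, the envelope may be opened at consent, and concealment ends at eligibility. None of these three statements makes completed baseline a condition for releasing the allocation, and no other passage does.

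**The plan's own figure.** Inputs from Sample size estimation: z values 1.64 and 0.84, SD 21.3, r = 0.81, difference 10.3, margin M = 4.26.

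N = 2 × (1.64 + 0.84)² × 21.3² × (1 − 0.81²) / (10.3 − 4.26)² = 2 × 6.1504 × 453.69 × 0.3439 / 36.48 = 52.6, so 53 per group. With 5% for losses this is 56 (53 × 1.05 = 55.7), and 3 × 56 = 168. The figure reproduces, and the present point does not change it.

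**Bias in the adjusted effect.** Suppose knowledge of the arm shifts reported baseline by *b* points in one arm and nothing else changes. The ANCOVA estimate then moves by slope × *b*, with sign opposite to the shift. The slope equals r × (SD at 3 months / SD at baseline). The article gives only a 1-year SD, so slope = 0.81 assumes equal SDs at the two times; 0.5 is shown as a lower alternative. The values of *b* are assumed, as the article offers none.

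| Assumed shift *b* | Bias, slope 0.81 | Share of M = 4.26 | Bias, slope 0.5 |
|---|---|---|---|
| 1 | 0.81 | 19% | 0.5 |
| 2 | 1.62 | 38% | 1.0 |
| 3 | 2.43 | 57% | 1.5 |
| 5 | 4.05 | 95% | 2.5 |

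At slope 0.81, a shift of 4.26 / 0.81 = 5.26 points would equal the whole margin.

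**What that does to the full-trial test.** With 53 per group, SE = 21.3 × √(1 − 0.81²) × √(2/53) = 2.43. At slope 0.81 and *b* = 2, the one-sided type I error is Φ(1.62/2.43 − 1.645) = 16.4% instead of 5.0% if the bias favours the programme. If it works against the programme, power is Φ((6.04 − 1.62)/2.43 − 1.645) = 57.0% instead of 80%. At *b* = 1 the figures are 9.5% and 69.5%. A simulation with 53 per group at *b* = 2 agreed (bias 1.68 points in size, type I error 16.8%).

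**Effect on r.** A uniform shift within an arm leaves the within-arm correlation unchanged. If r were pooled over three equal arms, a 3-point shift in one arm would add 3² × (1/3) × (2/3) = 2.0 to a variance of 453.7. Then r becomes 0.81 × √(453.7/455.7) = 0.808, which is negligible.

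**Room in the schedule.** 9 − 6 = 3 weeks between the earliest permitted enrolment and the start of the 6-week programme.

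**The case against.** Much of the case on the other side stands.

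- A reader might infer that every participant knows the arm when baseline is taken. The article does not say when participants are told, and the schedule figure is not shown. Disclosure before baseline is permitted and likely, not documented.
- A reader might infer that the pilot's results would be biased. The pilot's stated outcomes concern feasibility, and its analysis is descriptive with progression criteria. ANCOVA appears only in the sample size section for the later trial, and carrying pilot participants over is only a possibility.
- A reader might infer that the r taken from the pilot would be distorted. For a uniform shift the effect is trivial, as shown above. Selective loss could alter r, but nothing in the article allows that to be sized.
- The bias figures depend on assumed shifts confined to baseline. If the same shift persisted at follow-up, the net bias would be the follow-up shift minus slope × baseline shift: at slope 0.81, only 0.19 × *b*. Such cancellation would be accidental and could not be verified, so it does not justify the order. Equally, reordering does not remove reporting bias at follow-up, where participants still know their arm.
- The Blinding section's reference to testing can be read to include baseline, and the Trial design sentence on who performs the outcome measures is not limited to follow-up (the word describing the evaluator is an unfilled placeholder). On that reading goniometry is protected at baseline. A score supplied by the participant is not.

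The stated order and the missing safeguard survive these points.

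**Conclusion.** The point holds as a design weakness that should be fixed. The article randomises before baseline, allows the envelope to be opened at consent, and does not keep participants unaware of the arm until baseline is recorded. The consequence falls mainly on the full trial's baseline-adjusted SPADI comparison and on any pilot participants carried into it; for the pilot itself it is limited to randomised patients who leave before giving baseline data.

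The illustrative size is 0.8 to 4.1 SPADI points against the 4.26 margin. It rests on four assumptions: SPADI is completed by the participant (the article does not say so), the SDs at baseline and 3 months are equal, the shift is between 1 and 5 points, and the shift occurs at baseline only. The direction is unknown. The documents do not support the stronger conclusions that baseline data are certainly contaminated, that the pilot's progression decisions are compromised, or that the sample size of 53, then 56, per group is wrong.

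**What to change.** In Randomization and concealment of allocation, change the order to consent, then completion of all baseline measures, then opening of the envelope. Align the Trial design sentence on concealment, so that it ends only when eligibility is confirmed and baseline is recorded. If randomisation has to come first for logistical reasons, state instead that the allocation is withheld from both the participant and the baseline assessor until baseline is recorded.

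The inclusion criterion on surgery date already reserves about 3 weeks ahead of the programme for baseline measures, and the sample size is unaffected. The downside is a possible minor ethics amendment, since procedures are already approved. Whether the study visits need any rearrangement cannot be judged without the schedule figure.
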